## Abstract

**Introduction:**

Cystic fibrosis (CF) is commonly complicated by chronic rhinosinusitis (CRS). Despite highly effective management options, CRS in people with CF (PwCF+CRS) may be refractory to medical therapy, eventually requiring endoscopic sinus surgery. The impact of sinus surgery on pulmonary, quality of life (QOL), and other outcomes in PwCF+CRS in the expanding era of highly effective modulator therapy has not been fully elucidated. This study aims to determine if endoscopic sinus surgery can offer superior outcomes for PwCF+CRS when compared to continued medical treatment of CRS.

**Methods and analysis:**

This multi-institutional, observational, prospective cohort study will enroll 150 adults with PwCF+CRS across nine US CF Centers who failed initial medical therapy for CRS and elected to pursue either endoscopic sinus surgery or continue medical treatment. To determine if sinus surgery outperforms continued medical therapy in different outcomes, we will assess changes in pulmonary, CF-specific QOL, CRS-specific QOL, sleep quality, depression, headache, cognition, olfaction, productivity loss, and health utility value after treatment. The influence of highly effective modulator therapy on these outcomes will also be evaluated. This study will provide crucial insights into the impact of endoscopic sinus surgery for PwCF+CRS and aid with development of future treatment pathways and guidelines.

**Ethics and dissemination:**

This study has been approved by each institution’s internal review board, and study enrollment began August 2019. Results will be disseminated in conferences and peer-reviewed journals.

**Trial registration:**

This study was registered on ClinicalTrials.gov (NCT04469439).

## Introduction

Cystic fibrosis (CF) is a systemic disease with thick secretions affecting multiple organs, resulting in substantial health and economic burdens [1]. The leading cause of mortality in PwCF is pulmonary dysfunction, often due to secondary bacterial colonization from defective mucociliary clearance [2]. The unified airway theory suggests that similar infectious, inflammatory processes occur in both upper and lower airways, and upper airway infections may contribute to lower airway disease [1]. Most people with CF develop chronic rhinosinusitis (PwCF+CRS) from their inability to clear thickened secretions from the upper airways and paranasal sinuses, and most PwCF will demonstrate clinical or radiographic signs of sinonasal inflammation [3]. The Cystic Fibrosis Foundation (CFF) patient registry indicates that over half of adults report symptomatic sinus disease [4].

Endoscopic sinus surgery (ESS) is a treatment option for PwCF+CRS that serves to enlarge sinus openings, clear inspissated mucus, and facilitate application of topical therapies. Based on consensus guidelines, ESS is recommended for adults and children with CF with symptomatic CRS refractory to appropriate medical therapy [5, 6]. While ESS improves sinonasal symptoms and CRS-specific quality of life in PwCF+CRS [7], there is limited data evaluating ESS treatment outcomes in the era of highly effective modulator therapy (HEMT) and potential benefits of ESS in regions beyond the paranasal sinuses (**Fig 1**).

**Fig 1 pone.0310986.g001:**
[figure not shown]
Unaccounted factors in endoscopic sinus surgery decision-making for people with cystic fibrosis. ESS, endoscopic sinus surgery; CMT, continued medical therapy; PwCF+CRS, people with cystic fibrosis and comorbid chronic rhinosinusitis; CF, cystic fibrosis, CRS, chronic rhinosinusitis; QOL, quality of life; ppFEV_1_, percent of predicted expiratory volume in the first second.

The CF treatment landscape is rapidly transforming with the introduction of CF transmembrane conductance regulator (CFTR) modulator therapies. The triple combination therapy elexacaftor/tezacaftor/ivacaftor (ETI) is clinically available in the United States (US) for ~90% of people with CF > 2 years of age based on variant status and considered a HEMT [8]. ETI therapy has been associated with improved sinus computed tomography (CT) scan scores and CRS symptom severity, but does not fully resolve the symptoms of CRS in adults even with extended therapy for up to two years [9, 10]. While ETI has demonstrated high treatment efficacy, approximately 10% of people in the US are not eligible based on variant status and still others may not be able to tolerate the medication due to potential side effects [11]. Understanding the impacts of ESS in the modern era, while accounting for the effect of ETI, remains critical for the CF community.

Prior research on pulmonary outcomes after ESS has produced mixed results [12, 13], and has mainly consisted of small, retrospective studies. The current research landscape on ESS in PwCF is largely limited to retrospective case-control studies, constrained by patient numbers and the challenges of randomizing surgical interventions. This prospective, multi-institutional cohort-study aims to comprehensively determine the impact of ESS on PwCF+CRS in the era of highly effective modulator therapy.

## Materials and methods

### Study design, eligibility, and recruitment

This is a multi-institutional prospective, observational cohort study of patients electing to undergo either ESS or continued medical therapy (CMT) for CF-related CRS after having failed initial medical therapy. Patients will be enrolled at one of nine participating CF centers across the US.

Potential participants will be considered for study inclusion if they are adults (age 18–99 years), diagnosed with CF by genetic testing and/or sweat chloride testing, and have persistent CRS based on multi-disciplinary guidelines [5, 6]. Patients who underwent ESS in the 12 months preceding study enrollment, plan to have follow-up care at a non-participating institution, are unable to complete post-operative outcome measures, or started or modified new CFTR modulator therapy within 90 days of study enrollment will be excluded **(Table 1).** Participants consenting to study will be included in one of two study groups: those who elect to undergo ESS and those who pursue CMT. Extent of surgery, including use of extended approaches, will be tracked and analyzed.

**Table 1 pone.0310986.t001:** Inclusion and exclusion criteria.

Inclusion Criteria	Exclusion Criteria
Age 18 years or older	Underwent ESS in past 12 months
Diagnosed with CF as established by genetic testing combined with clinical assessment and/or sweat chloride	Will obtain follow up care at nonparticipating institutions
Diagnosed with CRS by multidisciplinary sinusitis guidelines	Unable to complete outcome measures
CRS symptoms persisting beyond initial medical treatment	Started new CFTR modulator therapy less than 90 days prior to screening or anticipated to begin during study period

ESS, endoscopic sinus surgery; CF, cystic fibrosis; CRS, chronic rhinosinusitis, CFTR, cystic fibrosis transmembrane receptor

All participants will be recruited from otolaryngology clinics at one of nine US institutions that are also CF Centers. Recruitment will occur at The University of California, Los Angeles (UCLA; Los Angeles, CA); University of Colorado (Aurora, CO); National Jewish Health (Denver, CO) including its affiliate Saint Joseph’s Hospital (Denver, CO); the University of Utah (Salt Lake City, UT); the Oregon Health and Science University (Portland, OR); the Medical University of South Carolina (Charleston, SC); the University of North Carolina (Chapel Hill, NC); Vanderbilt University Medical Center (Nashville, TN); and Stanford University (Palo Alto, CA); with UCLA as the coordinating site. Our recruitment goal is 150 patients. Recruitment techniques include routine face-to-face encounters, routine telephone encounters, and referrals from outside medical treatment facilities. An investigator or site coordinators using documents approved by each institution’s internal review board using Good Clinical Practice guidelines [14] will obtain written informed consent for all study participants.

### Objectives & endpoints

Objective 1: Determine whether ESS outperforms CMT for CF-related CRS over 12 months follow-up using endpoints of percent of predicted expiratory volume in the first second (ppFEV_1_), the rate of pulmonary exacerbations (PEx), and antibiotic utilization for exacerbations.Objective 2: Delineate changes in QOL and sinus-related comorbidities for participants who undergo ESS through 12 months of follow-up compared to CMT. Endpoints include assessing the impact of treatment on CF-specific QOL, CRS-specific QOL, sleep quality, depression, headache, cognition, and olfaction, which will be assessed using validated patient-reported outcome measures.Objective 3: Define changes in productivity loss (PL) and health utility value (HUV) in PwCF+CRS who undergo ESS through 12 months follow-up compared to standard CMT. Endpoints are validated patient-reported outcome measures to quantify PL and HUV.

All objectives will also evaluate the impact of ESS compared to CMT on pulmonary, rhinologic, QOL outcomes accounting for HEMT. Objectives and endpoints are listed in **Table 2**.

**Table 2 pone.0310986.t002:** Study objectives and endpoints in prospective observation study in adults with cystic fibrosis and comorbid chronic rhinosinusitis.

Objective	Endpoint	Assessments
1) Determine whether ESS outperforms CMT for CF-related CRS using measures in pulmonary function, the rate of PEx, and antibiotic use in over 12 months follow-up	Change in percent of predicted expiratory volume in the first second (ppFEV_1_) at initial visit and months 3,6,9, and 12.	NA
	Rate of PEx, and antibiotic utilization for exacerbations compared between treatment groups.	
2) Delineate changes in CF-specific quality of life and sinus-related comorbidities for subjects who undergo ESS through 12 months of follow-up and assess if ESS outperforms CMT in these areas.	Descriptive summary of CF-specific QOL, CRS-specific QOL, sleep quality, depression, headache, cognition, and olfaction; and improvement in scores and comparisons between groups from baseline through 12 months post-treatment.	CFQ-R (CF QOL), SNOT-22 (CRS QOL), PSQI (Sleep), PHQ-9-revised (Depression), HIT-6 (Headache), CFQ (Cognitive function), QOD (Olfaction), SIT (Smell Identification Test)
3) Delineate changes in productivity loss and health utility value for subjects who undergo ESS through 12 months of follow-up and evaluate if ESS outperforms CMT in these areas.	Descriptive summary of productivity and health utility value; and improvement in scores and comparisons between groups from baseline through 12 months post-treatment.	WPAI (Productivity), EQ-5D (Health Utility Value)

ESS, endoscopic sinus surgery; CMT, continued medical therapy; CF, cystic fibrosis, QOL, quality of life; ppFEV_1_, percent of predicted expiratory volume in the first second; PEx, pulmonary exacerbation; QOL, quality of life; CFQ-R, Cystic Fibrosis Questionnaire-Revised; SNOT-22, 22-question Sino-Nasal Outcome Test; PHQ-9-revised, Patient Health Questionnaire-9-revised; PSQI, Pittsburgh Sleep Quality Index; CFQ, Cognitive Failures Questionnaire; HIT-6, Headache Impact Test; QOD, Questionnaire of Olfactory Disorders; SIT, Smell Identification Test; WPAI, Work Productivity and Activity Impairment-Specific Health Problem; HUV, EQ-5D, 5-dimensional EuroQol questionnaire.

### Evaluation timeline

The following information will be collected at the patient’s initial consultation visit and 3, 6, 9, and 12 months follow-up with +/- 4-week ranges for follow up time points. These time points were selected based on the prior frequency that people with CF had routine clinic visits before the regulatory approval of ETI, as the study was designed in 2018.

Pulmonary function testing data that was obtained as clinical standard of care based on clinical records to analyze ppFEV1.PEx-related medical history and diagnostic testing; and data regarding utilization of oral and IV antibiotic utilizationQuestionnaires: Cystic Fibrosis Questionnaire-Revised (CFQ-R), 22-question Sino-Nasal Outcome Test (SNOT-22; © Washington University, St. Louis, MO), Pittsburgh Sleep Quality Index (PSQI), Patient Health Questionnaire-9-revised (PHQ-9-revised), Cognitive Failures Questionnaire (CFQ), and Headache Impact Test (HIT-6)Evaluations for olfactory function: 40-question Smell Identification Test (SIT; © Sensonics International, Haddon Heights, NJ) and the Questionnaire of Olfactory Disorders (QOD) for olfactory specific QOL assessmentProductivity loss and health utility data: Work Productivity and Activity Impairment-Specific Health Problem (WPAI) and 5-dimensional EuroQol questionnaire (EQ-5D-5L; © EuroQol Group, Rotterdam, The Netherlands) to quantify health utility value.

Mucus and nasal microbiome samples

A set of questions on attitudes regarding sinusitis will be completed once at the baseline visit. Data collection time points are identical for both ESS and CMT subjects and are further detailed in **Table 3.**

**Table 3 pone.0310986.t003:** Data collection time points in months.

Data collection time points	Baseline	3	6	9	12
History and physical, computed tomography	x				
Disease and socio-demographic factors	x				
Nasal endoscopy	x		x		
Treatment option: ESS vs. CMT	x				
Medication, CFTR modulator, cross-over data	x	x	x	x	x
PFTs, PEx data, antibiotic use	x	x	x	x	x
CFQ-R, SNOT-22, QOD, PSQI, PHQ-9-revised, CFQ, SIT, HIT-6, WPAI, HUV	x	x	x	x	x
Nasal mucus sponge, nasal microbiome swab	x	x	x	x	x
Blood, excised ethmoid sinus tissue*	x				

ESS, endoscopic sinus surgery; CMT, continued medical therapy; PwCF+CRS, people with cystic fibrosis and comorbid chronic rhinosinusitis; CF, cystic fibrosis, QOL, quality of life; CFTR, cystic fibrosis transmembrane receptor; PFT, pulmonary function test; PEx, pulmonary exacerbation; CFQ-R, Cystic Fibrosis Questionnaire-Revised; SNOT-22, 22-question Sino-Nasal Outcome Test; PHQ-9-revised, Patient Health Questionnaire-9-revised; PSQI, Pittsburgh Sleep Quality Index; CFQ, Cognitive Failures Questionnaire; HIT-6, Headache Impact Test; QOD, Questionnaire of Olfactory Disorders; SIT, Smell Identification Test; WPAI, Work Productivity and Activity Impairment-Specific Health Problem; HUV, health utility value; EQ-5D, 5-dimensional EuroQol questionnaire.

*These are for surgical cases only. Centers which routinely perform blood draws during clinic visits may also collect blood specimens at multiple follow up visits.

### Baseline measures

All participants will undergo baseline history and physical examination, CT, and nasal endoscopy. Key disease factors and potential predictors will also be obtained at initial visit with rhinologist. These include: age, gender, race/ethnicity, BMI, age at CF diagnosis, genotype, ppFEV1, CFTR modulator use details, prior ESS history, pancreatic insufficiency, *Pseudomonas* positivity, nontuberculous mycobacteria infection, lung transplantation status, insurance status, income, occupation, education, enrollment site, and medication use data. To measure CRS severity at baseline, we will use endoscopic and radiographic techniques. CT images will be scored via the Lund-Mackay system [15], and diagnostic nasal endoscopy will be performed and scored according to the Lund-Kennedy scoring system [16].

### Outcome assessments

To address objective 1, primary pulmonary outcome measure will be ppFEV_1_. Absolute values of FEV1 and FVC will be assessed as secondary spirometry measures, enabling evaluations of the FEV1/FVC ratio [17]. Forced expiratory flow at mid-lung volume (FEF25-75) is an important marker of small airway disease and will also be evaluated [18]. Secondary outcomes include the frequency of PEx (both outpatient and inpatient) and intravenous (IV) and oral antibiotic use. PEx will be defined by the Rosenfeld criteria [19]. The number of PEx, number of hospitalizations, and days of IV and oral antibiotics used will be tracked.

To address objective 2, quality of life outcome measures will include CFQ-R, evaluating CF-specific QOL [20], and the SNOT-22, evaluating QOL in subjects with CRS [21]. PHQ-9-revised will be used for depression screening [22], and the PSQI will measure sleep duration and quality [23]. CFQ will be used for cognitive assessment [24]. The HIT-6 will be utilized to determine headache severity [25]. For evaluation of olfactory function, we will use patient-reported and objective olfactory function tests. The QOD will assess the impact of olfactory dysfunction [26]. The SIT is a measure of objective olfactory function and complements the patient-reported QOD survey [27].

To address productivity loss and health utility in objective 3, the WPAI will be used to assess the impact of a specific health problem on normal work/school or daily activity [28]. Health utility value (HUV) will be quantified from the EQ-5D [29].

### Biospecimen collection

Biospecimens will be collected to assess nasal microbiology, inflammatory cytokines, and tissue histology, and analysis will investigate associations between biological findings and clinical outcomes. For both ESS and CMT groups, microbiome samples from the middle meatus will be obtained endoscopically. Nasal mucus specimens will be collected using sponges placed in the olfactory cleft for inflammatory cytokine analysis in both treatment groups.

For ESS patients, blood and excised tissue that would normally be removed during surgery from the ethmoid sinus will be collected at surgery. The tissue will be stored in a vial with RNAlater (Sigma Aldrich, MilliporeSigma, St. Louis, MO). Blood will be drawn during surgery using standard venipuncture techniques and collected in PAXGene Blood RNA tubes (Becton & Dickinson, Franklin Lakes, NJ). Centers which routinely perform blood draws during clinic visits may also collect blood specimens at multiple visits. All specimens will be collected at enrolling centers and will be transferred to one center for batch analysis to minimize variability.

### Statistical methods

For all objectives, we will verify predictive model assumptions and test goodness-of-fit, considering alternative models if needed. We will account for potential site-specific differences as fixed effects in our models. Other methods to address site clustering include mixed effects models and generalized estimating equations.

For Objective 1, mixed effects model will be used to assess the impact of ESS versus CMT on ppFEV_1_ changes at initial and subsequent visits. Fixed effects will include baseline FEV1 (FEV1 > 80% predicted, <80% and > 50%, and <50%), CF variant status, use of CFTR modulator therapy, sex, prior sinus surgery, time and treatment; patients will be treated as random effects. An unstructured variance approach will model within-subject errors, and we will explore other covariance if needed. As exploratory analysis, we will compare ppFEV_1_ from a year before enrollment to post-treatment values using the same model. Using a generalized linear model with a Poisson distribution and prior year data, we will assess the impact of ESS versus CMT on exacerbation rates and antibiotic use, complemented by descriptive statistics for sociodemographic factors.

For Objective 2, we will describe patient characteristics using summary statistics. Treatment effects on patient reported-outcome measures (CFQ-R, SNOT-22, PHQ-9, PSQI, CFQ, QOD, and SIT) will be explored via a mixed effects model, adjusting for multiple comparisons using a gate-keeping procedure and assessing for self-report bias in patient-reported outcomes by comparing them to FEV1.

For Objective 3, we will correlate productivity costs with patient demographics, disease factors, pulmonary status, and QOL impairment. We will use a mixed effects model to evaluate these outcomes.

Additionally, we will implement multiple approaches to compare changes in longitudinal treatment outcomes listed in objectives 1–3 between the ESS and CMT groups. First, multivariate Profile Analysis (MPA) [30], unlike the mixed model approach, can handle multiple variables simultaneously and does not require stringent assumptions. Two main effects from the MPA model are of interest: 1) Tests on patient group differences at baseline on the outcomes in the study and 2) tests of “parallelism”, determining if the outcome trajectories (or profiles) change similarly in the two patient groups over time. Second, we will apply Propensity Score Matching (PSM) to test for the causal effects of ESS and CMT on study outcomes, and to create balanced treatment comparisons to address self-selection biases [31, 32]. Other methods using propensity scores like weighting or stratification, and instrumental variable (IV) approach, will also be considered to adjust for potential biases and estimate causal effects.

Consideration was given to restricting enrollment to surgically naïve patients; however, this approach would limit enrollment. We will therefore explore subgroup analyses in surgically naïve study participants and sensitivity analyses to look at changes over time in outcomes. We also plan to account for surgical history in a mixed effects model that includes previous sinus surgery.

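### The Objective 1 model enters baseline FEV1 as three bands that omit exactly 80% and 50%; this costs precision and leaves some baseline imbalance in the estimate if ppFEV1 level is the response, which the wording does not exclude

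*Protocol article*

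**What the plan says.** The outcome for Objective 1 is continuous: "primary pulmonary outcome measure will be ppFEV_1" (Outcome assessments). It is also recorded at entry, in the list "age, gender, race/ethnicity, BMI, age at CF diagnosis, genotype, ppFEV1, CFTR modulator use details" (Baseline measures).

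The model is in Statistical methods: "mixed effects model will be used to assess the impact of ESS versus CMT on ppFEV_1_ changes at initial and subsequent visits". The covariate list begins "Fixed effects will include baseline FEV1 (FEV1 > 80% predicted, <80% and > 50%, and <50" (% predicted) and continues "CF variant status, use of CFTR modulator therapy, sex, prior sinus surgery, time and treatment; patients will be treated as random effects". It contains no continuous baseline term and names no treatment-by-time term.

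The groups are "those who elect to undergo ESS and those who pursue CMT" (Study design, eligibility, and recruitment). As further analyses, Statistical methods plans multivariate profile analysis, and propensity score matching "to create balanced treatment comparisons to address self-selection biases". Weighting, stratification and an instrumental variable are to be considered.

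**The concern.** There are two separate matters.

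- **The band edges.** Values of exactly 80 and exactly 50 are assigned to no band. This holds whatever the response is.
- **The use of bands at all.** Patients at 51 and 79 get the same baseline value. In a self-selected comparison the groups can differ inside a band, and the bands cannot adjust for that difference. Statistical power and sample size puts the detectable difference at 1.6 points, so a leftover bias of about one point would matter. A wider standard error would matter as well.

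How far the second matter bites depends on what the model takes as its response. Statistical methods speaks of changes, but includes the initial visit among the visits, where change from baseline is zero by definition. It lists time and treatment without an interaction. That could mean change from baseline, post-baseline levels, or all levels including the initial visit.

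**Working it through.** **The plan's own figure.** The article gives 80% power at two-sided 5% for 1.6 points with 170 participants and 20% dropout, so 170 × 0.8 = 136 analysed. It gives no SD, so the figure cannot be reproduced, only inverted. With equal groups (assumed), SD = 1.6 / (2.80 × √(4/136)) = 3.33. For the 2.3 points accounting for modulator therapy, SD = 4.79. These are small SDs. They suit a change or a baseline-adjusted value, not raw ppFEV1 within bands.

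**Assumed inputs (none is in the article).** Baseline mean 70; between-patient SD 20; visit-to-visit SD 5; 60 v 60; response based on the mean of four follow-up visits; no true effect; ESS group 5 points lower at baseline.

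**Formulae.**

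- Variance of a single baseline reading: 20² + 5² = 425. Slope of follow-up on baseline: λ = 400/425 = 0.941.
- Residual variance with continuous baseline: 400 × (1 - 0.941) + 25/4 = 29.8. SE = √(29.8 × 2/60) = 1.00.
- For a normal distribution with mean 70 and variance 425, cut at 50 and 80, the bands explain 79.6% of the baseline variance. They leave 425 × 0.204 = 86.6, a within-band SD of 9.3.
- Level with bands: 29.8 + 0.941² × 86.6 = 106.5. SE = √(106.5 × 2/60) = 1.88.
- Change with bands: the slope on baseline is λ - 1 = -0.059, so 29.8 + 0.059² × 86.6 = 30.1. SE = 1.00.
- Bias with continuous baseline: -5 × (1 - 0.941) = -0.29, the effect of visit noise in the baseline reading.

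**Simulation of the same set-up (6,000 replicates).**

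| Response | Baseline term | SE | Estimate when the truth is 0 |
|---|---|---|---|
| Level | bands | about 1.9 | about -1.25 |
| Level | continuous | 1.0 | -0.3 |
| Change | bands | 1.01 | -0.24 |
| Change | continuous | 1.00 | -0.30 |
| Change | none | 1.02 | 0.00 |

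On the level response, 1.25/5 = 25% of the imbalance remains, so the bands remove about 75%. With a linear continuous baseline the level and change rows agree, because subtracting a covariate already in the model leaves the treatment coefficient unchanged.

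**Sensitivity to the assumptions.** Baseline mean was varied over 65 to 80, SD over 20 to 22 and baseline-to-follow-up correlation over 0.90 to 0.97.

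- Level: residual variance with bands is 1.8 to 5.1 times that with continuous baseline. A 5-point imbalance leaves 0.9 to 1.3 points.
- Change: the variance ratio is 1.003 to 1.013, and at most 0.14 points are left.

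**Random-intercept mixed model.** Assumptions: 136 patients, five visits, within-patient SD 3.5, 60 replicates. Differences detectable with 80% power:

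- post-baseline level, treatment main effect: 4.7 points with bands, 1.9 with continuous baseline;
- change: 1.91 with bands, 1.89 with continuous baseline;
- initial visit in the outcome vector, treatment-by-time contrast: 1.88 with either.

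**Band edges.** If ppFEV1 is recorded in whole numbers (not stated), 2.7% to 3.0% of patients would sit on 50 or 80 under these distributions. That is 150 × 0.027 to 150 × 0.030, about 4 to 5 patients.

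**The case against.** The strongest reply is that the article mostly speaks of change: in Table 2, in the model sentence and in the power statement. On a change response the precision loss disappears. Continuous baseline does not reduce bias there either (-0.30 against -0.24 with bands). This stands, and it makes the precision and bias claims conditional. It does not remove them, because naming the initial visit and listing only time and treatment leave the level reading open.

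A reader might infer that baseline imbalance goes uncorrected. The article does not support that. Even in the least favourable reading the bands remove about three quarters of it, and propensity and profile analyses are planned against self-selection. Those analyses are additional, however, and do not alter this model.

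A reader might also infer that banding wastes precision whatever the response, or set the leftover 1.25 points directly against the 1.6-point target. Neither follows. The first fails for change and for treatment-by-time. In the second, the SD implied by 1.6 points fits change or adjusted values, so the bias and the target may belong to different models.

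Finally, the edges may be called a drafting slip that a coding specification would close. That is fair as to size, and the article does not say such patients would be dropped. But the article itself fixes the bands, so this is not detail left to an analysis plan. Its allowance for alternative models depends on fit checks and does not close the gaps.

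**Conclusion.** The point holds in a limited form. Certain from the text: the bands leave out exactly 80% and exactly 50%, and they discard within-band information on the outcome's own baseline in a self-selected comparison.

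Conditional: if ppFEV1 level is modelled with a treatment main effect, the standard error is roughly doubled (about 1.9 against 1.0) and about a quarter of any baseline imbalance remains in the treatment effect. If the response is change from baseline, or baseline is in the outcome vector with a treatment-by-time contrast, the precision cost is negligible and continuous baseline brings no reduction in bias.

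All sizes rest on assumed means, SDs, correlations, group split and imbalance. The change is still worth making, because the wording does not settle which case applies and the bands cost little in some cases and a great deal in another.

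**What to change.** State the response, and let the baseline term follow from it. Either:

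1. take the post-baseline visits as the response, with baseline ppFEV1 as a continuous covariate (linear or restricted cubic spline); or
2. keep the initial visit in the outcome vector, estimate the effect by a treatment-by-time contrast, and do not also use baseline as a covariate, so that one measurement is not both covariate and response.

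Keep the bands for descriptive tables or subgroups only, with closed edges, for example ≥80, 50 to <80, and <50.

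The cost is a line or two in the analysis plan. The value is already collected, and no extra data or patients are needed. Enrolment was still open at the last stated status (87 participants in October 2023).

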### Patient retention and missing data analysis

Missing data will be presumed to be missing at random (MAR). For our primary analyses, we will use mixed effects model to handle missing data issues based on MAR using Full Information Maximum Likelihood (FIML) estimation.

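### The primary ppFEV1 model lists no measure of current sinus disease severity, although three are collected at baseline, so the ESS v CMT estimate is at risk of confounding by indication

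*Protocol article*

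**What the plan says.** The design section describes a "prospective, observational cohort study of patients electing to undergo either ESS or continued medical therapy (CMT"), so treatment is not randomised. For Objective 1, Outcome assessments states that the "primary pulmonary outcome measure will be ppFEV_1".

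The Statistical methods section gives the covariates of the ppFEV1 mixed model. The list opens with "Fixed effects will include baseline FEV1 (FEV1 > 80% predicted, <80% and > 50%, and <50" per cent) and continues with "CF variant status, use of CFTR modulator therapy, sex, prior sinus surgery, time and treatment". Site is added as a fixed effect, and patients are random effects. The section on missing data makes this the leading analysis: "For our primary analyses, we will use mixed effects model to handle missing data issues based on MAR".

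The Baseline measures section says: "To measure CRS severity at baseline, we will use endoscopic and radiographic techniques". These are the Lund-Mackay CT score and the Lund-Kennedy endoscopy score. Table 3 shows SNOT-22 at baseline. Baseline measures also lists age, Pseudomonas and transplantation status among the factors recorded. Prior-year data are used in the Poisson model for exacerbations and antibiotics.

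Self-selection is taken up later in Statistical methods, among further analyses. Propensity score matching is to be applied "to create balanced treatment comparisons to address self-selection biases". Weighting, stratification and instrumental variables are named as options to be considered.

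**The concern.** When patients and surgeons choose the treatment, the reasons for the choice can also predict the outcome. The Introduction supplies both links for sinus severity. It cites guidance that recommends ESS when CRS remains symptomatic despite medical therapy, so symptoms are part of the indication. It also holds that upper airway infection may feed lower airway disease, which is the reason to expect ESS to affect ppFEV1 at all. A variable with both links is a candidate confounder of the ESS v CMT comparison. In the primary model its only representative is prior sinus surgery, which records history and not present severity.

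If the groups differ in severity, part of the primary treatment coefficient could reflect that difference. Should the propensity analysis then disagree, the article gives the mixed model the primary place.

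**Working it through.** **Covariate check.** Baseline variables against the listed ppFEV1 fixed effects:

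| Variable | Collected at baseline | Listed in ppFEV1 model |
|---|---|---|
| FEV1 | yes | yes, three bands |
| CF variant, modulator use, sex, prior ESS, site | yes | yes |
| Lund-Mackay, Lund-Kennedy | yes | no |
| SNOT-22 | yes | no |
| Age, Pseudomonas, transplantation status | yes | no |
| Prior-year exacerbations | yes (Poisson model) | no |

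**The plan's own yardstick.** The power section states 80% power to detect 1.6% ppFEV1 with 170 participants and 20% dropout, two-sided 5%. Evaluable patients: 170 × 0.8 = 136. The 1.6 cannot be reproduced, because no SD, allocation ratio or within-patient correlation is given. It can only be solved backwards. I assume 1:1 groups of 68 and read 1.6 as a between-group difference in change:

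- Implied SD = 1.6 / [(1.960 + 0.842) × √(4/136)] = 1.6 / (2.802 × 0.1715) = 3.33 points.
- Standard error of the group difference = 3.33 × √(2/68) = 0.571 points.

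**Size of bias under assumptions.** Bias = (ppFEV1 points per SD of severity, given the listed covariates) × (group imbalance in SD). The false-positive rate at nominal 5% is Φ(bias/0.571 − 1.96) + Φ(−bias/0.571 − 1.96). Neither input to the bias is in the documents, so a range is shown:

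| Points per SD | Imbalance (SD) | Bias (points) | Share of 1.6 | False-positive rate |
|---|---|---|---|---|
| 0.5 | 0.2 | 0.10 | 6.25% | 5.4% |
| 0.5 | 0.5 | 0.25 | 15.6% | 7.2% |
| 0.5 | 0.8 | 0.40 | 25% | 10.8% |
| 1 | 0.2 | 0.20 | 12.5% | 6.4% |
| 1 | 0.5 | 0.50 | 31.25% | 14.1% |
| 1 | 0.8 | 0.80 | 50% | 28.8% |
| 2 | 0.2 | 0.40 | 25% | 10.8% |
| 2 | 0.5 | 1.00 | 62.5% | 41.7% |
| 2 | 0.8 | 1.60 | 100% | 80.0% |

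On the implied SD, slopes of 0.5, 1 and 2 points correspond to correlations of about 0.5/3.33 = 0.15, 1/3.33 = 0.30 and 2/3.33 = 0.60 between severity and ppFEV1 change. The last is strong, so the bottom rows mark an upper end and not an expectation.

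**How much the FEV1 bands do.** In a simulation with baseline ppFEV1 assumed normal (mean 65 to 75, SD 20 to 22), the three bands explain about 78% to 81% of its variance. A raw group difference of 5.8 to 10.4 points shrinks to about 1.2 to 2.3. Baseline lung function is thus largely, though not fully, adjusted for. Current sinus severity has no comparable term.

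**The case against.** Several points on the other side are sound.

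- A reader might infer that lung disease is left out. It is not: banded baseline FEV1 is in the model, with CF variant, modulator use and site. What is absent is current CRS severity and some further markers.
- A reader might infer that self-selection is ignored, or handled only by one-to-one matching. The article commits to propensity matching for the outcomes of all three objectives, names weighting as an option and states no matching ratio. The multivariate profile analysis also tests baseline group differences in the outcomes, but as described it does not adjust for sinus severity. Unnamed propensity covariates are what a condensed article leaves to the full plan, and are not criticised here.
- A reader might extend the point to every outcome. No covariate list is given for Objectives 2 and 3, so no omission can be shown there.
- A reader might conclude that the estimate is confounded, or that ESS patients are the sicker group. The documents do not say what drives the choice and report no imbalance. Both groups must have CRS persisting after initial treatment, which may narrow the gap.
- The list is introduced as what the fixed effects will include, and alternative models are allowed for, so it may not be exhaustive.

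These limit the scope and size of the point. They do not remove it: the article does name the covariates of its primary model, no severity score is among them, and the propensity work that could compensate is secondary.

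**Conclusion.** The point holds for the primary ppFEV1 analysis and should be fixed. In a self-selected comparison, the listed model adjusts for no current measure of the disease that surgery treats, although three such measures are available. The result is a risk of confounding by indication, not a demonstrated bias, and its direction is unknown. Its size depends on assumptions about slope and imbalance: from negligible (0.1 points) to as large as the 1.6-point target, with 0.25 to 1.0 points at a 0.5 SD imbalance. The false-positive rates also rest on 1:1 allocation, 136 evaluable patients and an SD solved back from the plan's own power statement. The planned propensity analysis reduces the concern without settling it, because it does not produce the primary estimate.

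**What to change.** Add baseline Lund-Mackay, Lund-Kennedy and SNOT-22, together with age, Pseudomonas, transplantation status and prior-year exacerbation count, to the fixed effects of the primary ppFEV1 model. Use the same set in the propensity analysis already planned, so that the two estimates differ by method and not by covariates. If the initial visit stays among the modelled responses, let the severity scores interact with time as well, since a main effect alone adjusts the level of ppFEV1 and not its change.

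The cost is a change of wording, with no new data collection. Seven terms entered as single continuous or yes/no variables use about seven degrees of freedom, against 150 × 0.8 = 120 to 170 × 0.8 = 136 evaluable patients. Interactions of the three scores with five categorical visits would add 3 × 4 = 12 parameters. The article reports that enrolment was still under way, so the list can be fixed before the outcome data are analysed.
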